**Methods:**

A two-arm parallel randomized controlled trial is conducted in a target sample of 285 non-suicidal Hong Kong Chinese older than 17 years of age with major depression and insomnia. Participants complete an online rapid screening, followed by a telephone diagnostic interview. Those who meet the eligibility criteria are randomized in a ratio of 1:1 to receive either CBT-I immediately or to a waitlist control condition. The CBT-I consists of six weekly modules and is delivered through a smartphone application proACT-S. This smartphone app has been pilot tested and revamped to improve user experience. An online randomized algorithm is used to perform randomization to ensure allocation concealment. The primary outcomes are changes over the measurement points in sleep quality, insomnia severity, and depression severity. The secondary outcomes include changes over the measurement points in anxiety, subjective health, treatment expectancy, and acceptability of treatment. Assessments are administered at baseline, post-intervention, and 6-week follow-up. The recruitment is completed. Important adverse events, if any, are documented. Multilevel linear mixed model based on intention-to-treat principle will be conducted to examine the efficacy of the CBT-I intervention.

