## Objectives

This paper describes the protocol for a two-arm parallel RCT study that compares the efficacy of a smartphone-based self-help CBT-I with a waitlist control group in treating people with MDD and insomnia in Hong Kong. It is hypothesized that, after the intervention, participants in the CBT-I condition will report a greater decrease in poor sleep quality, depression severity, and insomnia severity than those in the waitlist control condition. It is also hypothesized that the reduction in poor sleep quality, depression severity, and insomnia severity observed in the CBT-I condition will be maintained at 6-week follow-up. Furthermore, it is hypothesized that participants in the waitlist control condition will report a significant decrease in poor sleep quality, depression severity, and insomnia severity after receiving CBT-I.

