### Data analysis plan

The principle of intention-to-treat analysis will be adopted, in which all randomized participants with missing observations, from lost to follow-up or incomplete outcome assessments, will be handled by multiple imputation [53]. Missing data is assumed to be 5%.

Chi-square tests and independent *t* tests will be conducted to examine if participants in the CBT-I and waitlist control conditions differ in terms of demographic characteristics, clinical comorbidity, and baseline outcome scores. Multilevel linear mixed model based on the intention-to-treat principle will be used to calculate between-condition mean differences in the primary outcome changes in sleep quality, insomnia, and depression severity from baseline to post-intervention assessments. Multilevel linear mixed model based on the intention-to-treat principle will also be used to analyze secondary outcomes of the baseline to post-intervention change in subjective health and anxiety between CBT-I and waitlist control conditions. Clustering effect, significant baseline differences in demographics, clinical characteristics, and outcome variables will be adjusted for. Pair-sample *t* tests based on the intention-to-treat principle will be used to analyze changes in primary outcomes, subjective health, and anxiety obtained at post-intervention and 6-week follow-up separately for each condition. All comparisons are planned with a 5% two-sided significance level. Bonferroni adjustment will be applied.

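### Bonferroni is promised without naming the tests it covers, while the sample size gives each of three primary outcomes an unadjusted 5%; the two sections do not agree

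*Protocol article*

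**What the plan says.** The Data analysis plan lists three groups of efficacy tests.

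- **Primary, between conditions:** a mixed model for "between-condition mean differences in the primary outcome changes in sleep quality, insomnia, and depression severity from baseline to post-intervention assessments".
- **Secondary, between conditions:** the same model for "secondary outcomes of the baseline to post-intervention change in subjective health and anxiety between CBT-I and waitlist control conditions".
- **Within condition:** paired t tests, which "will be used to analyze changes in primary outcomes, subjective health, and anxiety obtained at post-intervention and 6-week follow-up separately for each condition".

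Two sentences close the section: "All comparisons are planned with a 5% two-sided significance level. Bonferroni adjustment will be applied". The first sets the level. The second does not say to which tests it applies.

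Two other places affect which tests might count as primary. The Abstract is looser about time points: "The primary outcomes are changes over the measurement points in sleep quality, insomnia severity, and depression severity". The Objectives state three hypotheses without ranking them. The second is maintenance of gains in the CBT-I condition, and the third concerns the waitlist after treatment: "Furthermore, it is hypothesized that participants in the waitlist control condition will report a significant decrease in poor sleep quality, depression severity, and insomnia severity".

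The Sample size section works at a two-sided alpha of 0.05 with 80% power, Cohen's f = 0.2 and 12 covariates. It arrives at 199 evaluable participants, or 285 after 30% attrition, and makes the power claim for each of the three primary outcomes separately.

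**The concern.** A Bonferroni rule is defined by its divisor. If the family is not named, the text does not fix the p-value at which a primary outcome counts as a success. A primary p-value of 0.008 would pass with divisor 3 (0.0167) and fail with divisor 15 (0.0033).

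The analysis rule and the sample size also pull in different directions. The sample size spends a full 5% on each of three primary outcomes. Any Bonferroni family that holds all three gives each of them at most a third of that. Either the power statement is too favourable, or the adjustment is not meant for the primary tests and three primary outcomes are each tested at 5%. A reader cannot tell which.

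If the wider family were used, the randomised comparisons would share their error budget with secondary outcomes and with before-after tests that have no control group. That would cost power on the question the trial was built to answer.

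**Working it through.** **Inputs.** From Sample size: f = 0.2, two-sided alpha 0.05, 80% power, 12 covariates, 199 evaluable, 30% attrition, total 285. From Data analysis plan: the tests listed, Bonferroni, and 5% missing data. Assumptions made here: f = 0.2 holds for all three primary outcomes and, for Holm, their test statistics correlate at 0.5.

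**1. Reproduce the plan's figure.** The ANCOVA F test has noncentrality λ = f²N, numerator df 1 and denominator df N − 2 − 12. With N = 199, λ = 0.04 × 199 = 7.96 and the denominator df is 185. At alpha 0.05 power is 80.1%, and 199 is the smallest N that reaches 80%. Then 199/0.70 = 284.3, so 285. The plan's figures therefore reproduce at an unadjusted 5%.

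**2. Count the listed efficacy tests.**
- Primary, between conditions: 3. Threshold 0.05/3 = 0.0167.
- Adding the two secondary between-condition tests: 3 + 2 = 5. Threshold 0.05/5 = 0.0100.
- Adding paired tests of five measures in each of two conditions: 5 + 5 × 2 = 15. Threshold 0.05/15 = 0.0033.
- If the SF-12 physical and mental scores are tested separately: 6 + 6 × 2 = 18. Threshold 0.05/18 = 0.0028.

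**3. Power per primary outcome at each threshold, same formula.** The plan's 5% missing data gives 285 × 0.95 = 270.75, about 271 observed.

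| Divisor | Threshold | 199 evaluable | 271 observed | All 285 |
|---|---|---|---|---|
| 1 | 0.05 | 80% | 91% | 92% |
| 3 | 0.0167 | 66% | 81% | 83% |
| 5 | 0.0100 | 59% | 76% | 78% |
| 15 | 0.0033 | 44% | 63% | 66% |
| 18 | 0.0028 | 42% | 61% | 64% |

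To keep 80% power after 30% attrition, divisor 3 needs 265 evaluable (265/0.70, rounded up to 379 in total). Divisor 15 needs 362 (518 in total).

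**4. The reading that leaves the primary tests at 0.05.** The 80% claim then stands, but the chance of at least one false positive among the three primary tests, if all nulls hold, is 1 − 0.95³ = 14.3% under independence. At a correlation of 0.5 it is 12.6% by simulation.

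**5. Holm on the three primary contrasts.** The smallest p-value is compared with 0.05/3, the next with 0.05/2 and the largest with 0.05, stopping at the first failure. Simulating three test statistics with noncentrality √7.96 = 2.82 and correlation 0.5 gives 73.5% power per outcome, against 65.7% for Bonferroni. For correlations from 0.3 to 0.7 the Holm figure stays between about 73% and 74%. The family-wise guarantee is the same.

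**The case against.** The strongest reply is that the article condenses a fuller document. The divisor is the kind of detail commonly left to a full protocol or SAP, and neither is shown. The primary contrast is also recognisable: both the Sample size section and the Data analysis plan tie the primary outcomes to between-condition change from baseline to post-intervention, and subjective health and anxiety are labelled secondary. A family of three is therefore the natural reading. This stands, and the unnamed divisor alone would be a small matter. It does not remove the disagreement between sections, because both the power claim and the adjustment are stated in this document.

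A reader might infer more than the text supports:

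- **That the plan prescribes a 15-test family.** It does not. The words about all comparisons belong to the sentence on the 5% level, and the Bonferroni sentence has no object. Fifteen is one possible reading.
- **That the trial would probably miss a true effect of the planned size.** This follows only if divisor 15 and 30% loss hold together (44%). With the plan's own 5% missing data, power is 63% even at divisor 15.
- **That the family will be chosen after the p-values are seen.** The text does not prevent this, but a SAP that fixes the family may exist.
- **That the false-positive rate is far above 5% over 9 or 15 unadjusted tests.** The plan says an adjustment will be made. A rate for those families also needs a correlation structure that the documents do not give, and equal correlation is unrealistic because paired tests in the two arms use different people.

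Bonferroni is also a valid method, so preferring Holm corrects no error. It is recommended because it recovers power at no cost in error control.

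**Conclusion.** The concern holds in this limited form. The Data analysis plan commits to Bonferroni without naming a family, and the Sample size section claims 80% power per primary outcome at a level that no Bonferroni family containing all three would allow. On the natural reading, power per outcome is about 66% at 199 evaluable. It is about 81% if only 5% of data are missing, so the shortfall depends on which of the plan's two loss assumptions (30% attrition or 5% missing) comes true. The widest readings lower these figures to 44% and 63% with 15 tests. The narrowest reading restores the stated 80% but leaves three primary tests at 5% each.

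These figures rest on f = 0.2 for all three outcomes and on the plan's ANCOVA model rather than the mixed model that will be fitted. They treat imputed values as adding no information.

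**What to change.** Before the analysis, in a dated statement or the SAP:

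1. Define the confirmatory family as the three between-condition differences in change from baseline to post-intervention (ISI, PSQI, CES-D), tested by the Holm procedure at a family-wise two-sided 5%.
2. Place subjective health, anxiety and all within-condition comparisons outside this family, and report them with 95% confidence intervals.
3. Align the Abstract's description of the primary outcomes with this contrast.
4. Restate the power in the Sample size section at the adjusted level: at 199 evaluable, about 74% per outcome with Holm, or about 66% if plain Bonferroni is kept, with the assumptions named (f = 0.2 for all three and, for Holm, correlation 0.5).

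If the sponsor prefers Bonferroni, naming the family with divisor 3 also resolves the ambiguity; only the restated power differs.

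The cost is wording: no new data and no further participants. Recruitment is complete, but the article describes the analyses as still to come. There are two downsides. The maintenance hypothesis and the waitlist within-condition hypothesis in the Objectives are no longer confirmatory, and the stated power becomes less favourable.

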### Sample size

The most updated meta-analysis of 28 self-help CBT-I RCTs [19] showed a significant treatment effect in alleviating depressive symptoms (Hedges’ *g* = 0.35) and insomnia symptoms (Hedges’ *g* = 0.79). It also found that the mean cumulative study attrition rates were 21.25% (SD = 15.31%) and 18.4% (SD = 18.21%) in the treatment and the waiting list/routine care/no treatment/psychoeducation groups, respectively. Hence, a conservative small effect size (Cohen’s *f* = 0.2) and an attrition rate of 30% are estimated for the present study.

The sample size calculation for each of the three primary outcomes (i.e., insomnia severity, poor sleep quality, and depression severity) is based on mixed ANCOVA using GPower 3.1. To conduct a 2 (condition: CBT-I versus waitlist control) × 2 (assessment: baseline versus post-intervention) mixed ANCOVA with an alpha value set at 0.05, two-sided, 80% power to detect a small effect of 0.2 (Cohen’s *f*) between two groups while controlling for 12 covariates (demographics, clinical comorbidity, treatment expectancy, and acceptability of treatment), a total sample size of 199 will be required. In order to account for 30% attrition, a total sample of 285 participants will be sufficient to detect a small effect size (Cohen’s *f* = 0.2) for the difference in the change in each of the three primary outcomes (i.e., insomnia severity, poor sleep quality, and depression severity) from baseline to post-intervention between CBT-I condition and waitlist control condition with a two-sided 5% significance level and a power of 80%.

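### The 80% power stated for each primary outcome is computed at an unadjusted 5% level, but the analysis plan applies a Bonferroni adjustment that the sample size ignores

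*Protocol article*

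**What the plan says.** Protocol article, Sample size: the calculation is made separately per outcome ("The sample size calculation for each of the three primary outcomes"), "with an alpha value set at 0.05, two-sided, 80% power to detect a small effect of 0.2" in Cohen's f, "while controlling for 12 covariates". The result is that "a total sample size of 199 will be required". The section continues: "In order to account for 30% attrition, a total sample of 285 participants will be sufficient" to detect that effect "for the difference in the change in each of the three primary outcomes", and it restates the two-sided 5% level and 80% power for the final number. It does not mention multiplicity.

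Protocol article, Data analysis plan: the primary analysis is a between-condition comparison of baseline-to-post change in sleep quality, insomnia and depression. Subjective health and anxiety are analysed the same way as secondary outcomes, and paired t tests are done within each condition. The section closes with "All comparisons are planned with a 5% two-sided significance level. Bonferroni adjustment will be applied". It names neither the family nor the per-test level. The same section assumes 5% missing data, whereas Sample size plans for 30% attrition.

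**The concern.** Power is a property of a test at a given significance level. Sample size gives the power of each primary test at 0.05. The Data analysis plan applies Bonferroni with no exception for the primary contrasts, so on its plain wording those tests run at a stricter level. The stated 80% then belongs to a test that will not be performed.

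Type I error is not at risk, because Bonferroni protects it. What is at stake is how a non-significant result is read: it would be taken as coming from an 80%-powered comparison. Depression is the most exposed outcome. Sample size cites a prior effect of g = 0.35 for it, which is below the d = 0.40 implied by f = 0.2.

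**Working it through.** **Inputs, all from Sample size unless noted.** Two arms at 1:1 (Trial design); f = 0.2, which is d = 2f = 0.40 for two equal groups; 12 covariates; two-sided alpha 0.05; target power 80%; attrition 30%; three primary outcomes. Bonferroni comes from the Data analysis plan. The family size is an assumption: three for the main case, five as a sensitivity case.

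**Formula.** ANCOVA F test: df1 = 1, df2 = N − 2 − 12, noncentrality λ = N·f². Power = P(F′(df1, df2, λ) > F critical at 1 − alpha).

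**Step 1: reproduce the stated figures.** At N = 199, df2 = 185 and λ = 199 × 0.04 = 7.96. At alpha 0.05 the critical F is 3.89 and power is 0.801. At N = 198 power is 0.799, so 199 is the smallest N that reaches 80%. Inflation: 199 / 0.70 = 284.3, rounded up to 285. Both figures match, which confirms that the sizing used an unadjusted 0.05.

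**Step 2: apply the adjustment, family of three.** alpha = 0.05/3 = 0.0167. With the same df2 and λ, the critical F is 5.84 and power is **0.657**. The effect detectable with 80% power rises from f = 0.20 to f = 0.231 (d from 0.40 to 0.46).

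**Step 3: sensitivity to the number analysed** (285 randomised, alpha 0.0167, f = 0.2).

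| Attrition or missing data | Source | N analysed | Power |
|---|---|---|---|
| 30% | Sample size, planning value | 199 | 0.66 |
| 21.25% | Sample size, cited mean, treatment arms | 285 × 0.7875 → 224 | 0.72 |
| 18.4% | Sample size, cited mean, control arms | 285 × 0.816 → 232 | 0.74 |
| 5% | Data analysis plan | 285 × 0.95 → 270 | 0.81 |

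The two cited rates are arm-specific. Each is applied here to the whole sample, so a mixture of them falls between 0.72 and 0.74.

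**Step 4: sensitivity to the family.** If the family is the five outcomes named for the mixed model (three primary, subjective health, anxiety), alpha = 0.05/5 = 0.01. The critical F is 6.77 and power at N = 199 is 0.587.

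**Step 5: by outcome, using the cited effects** (f = g/2, N = 199). Depression, g = 0.35: power 0.69 at 0.05 and 0.52 at 0.0167. Insomnia, g = 0.79: above 0.99 at both levels.

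**Step 6: size that would have met the claim.** At alpha 0.0167, 80% power at f = 0.2 needs 265 evaluable (power 0.800); 265 / 0.70 = 378.6, so 379 randomised.

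**The case against.** **The family is not stated, and an article may leave it to a fuller document.** This is fair, and it is why 66% is conditional. If Bonferroni covered only the within-condition paired t tests, the 80% would stand. But the sentence directly follows one about all comparisons and carries no such limit. The point is also not about missing detail: a stated power and a stated adjustment in the same document do not fit together.

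**The number analysed may exceed 199.** This also stands. Under the 5% missing data in the Data analysis plan, adjusted power is about 81%. However, Sample size rests its own 80% on 30% attrition, and the document cannot rely on one figure for sizing and the other for power.

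**Tempting stronger readings.** A reader might infer that the design simply delivers 66%. The documents do not support an unconditional figure, because it needs a family of exactly three and 199 analysed. A reader might also infer that the two closing sentences of the Data analysis plan contradict each other. They read naturally as a familywise 5% followed by an adjustment, which is loose but consistent. Finally, 66% is power per outcome, not the chance that at least one of the three is significant.

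**The practical consequence is limited.** This is correct. Error control is intact, insomnia keeps near-full power at the cited effect, and recruitment is closed. What needs correcting is a design claim.

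**Conclusion.** The point holds in conditional form. Sample size states 80% power per primary outcome at a level that the analysis plan does not, on its wording, use for those outcomes. The published arithmetic is right at unadjusted 0.05; the inconsistency lies in the alpha.

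On the sizing section's own inputs (f = 0.2 and 199 analysed), and assuming a family of the three primary contrasts, power is about 66%, some 14 percentage points below the claim (80.1% − 65.7%). The range for that family is 66% to 81%, depending on which of the article's own attrition or missing-data figures applies. It reaches 80% only under the 5% missing-data assumption. A wider family lowers it further.

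**What to change.** 1. **Data analysis plan.** Name the three primary baseline-to-post between-arm contrasts as the Bonferroni family, at familywise two-sided 5% (0.0167 each). State that the within-arm tests serving the hypotheses in Objectives (maintenance in the CBT-I arm, improvement in the waitlist arm after treatment) lie outside that family. They should stay as tests, since two of the stated hypotheses depend on them.
2. **Sample size.** Restate the power at 0.0167: about 66% for f = 0.2 with 199 evaluable, detectable effect about f = 0.23.
3. **Both sections.** Reconcile 30% attrition with 5% missing data, and give the power for the figure that is kept.

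Holm is an optional replacement for Bonferroni, not a needed correction. If it is adopted, the restated power must be Holm's, with the assumed correlation between outcomes given. As an illustration, three equal effects of d = 0.40 with an assumed correlation of 0.5, which is not in the article, give about 74% per outcome.

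The cost is wording and a less favourable stated power. Recruitment is complete (Recruitment; Trial status), and no change in enrolment is needed. The family should be fixed before the outcome data are analysed, so that it cannot be chosen in the light of results.

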## Methods

### Trial design

This is a two-arm, with equal randomization (1:1 allocation ratio) parallel, superiority RCT. It compares a self-help smartphone-based CBT-I intervention to a waitlist control condition. The self-help treatment is delivered through “proACT-S,” a smartphone application developed by the corresponding author’s research team. The results from a pilot study showed that proACT-S was efficacious for treating insomnia and was positively received by the users [23]. The current RCT is designed to test the efficacy of proACT-S in treating people with MDD and insomnia. Participants’ change in depressive and insomnia symptoms after the CBT-I intervention will be compared with that of the waitlist control group. The rationale for choosing waitlist control as the comparison condition is twofold: (1) it allows researchers to determine the effect of the intervention against not receiving treatment during the trial period and (2) it ensures that all participants will eventually receive the treatment.

Prior to trial entry, participants complete a two-stage screening. Their eligibility is assessed by an online survey, followed by a telephone diagnostic interview. After the two-stage screening, the assessments, randomization, and intervention are carried out via proACT-S. The research design is summarized in Fig. 1. The full SPIRIT checklist is provided as Additional file 1.

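### If the planned Bonferroni adjustment covers the three primary contrasts, it is valid, but Holm's step-down procedure gives more power at the same 5% familywise error

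*Protocol article*

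**What the plan says.** All references are to the protocol article.

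- **Data analysis plan.** The between-condition changes from baseline to post-intervention in sleep quality, insomnia and depression are tested with a multilevel linear mixed model. The same paragraph covers between-condition tests of subjective health and anxiety, and paired t tests within each condition. It sets a two-sided 5% level for all comparisons and then states: "Bonferroni adjustment will be applied". It does not say which tests form the family, what the divisor is, or whether a stepwise version is meant.
- **Sample size.** "The sample size calculation for each of the three primary outcomes" uses "an alpha value set at 0.05, two-sided, 80% power to detect a small effect of 0.2" (Cohen's f), "while controlling for 12 covariates". The result is that "a total sample size of 199 will be required". The section continues: "In order to account for 30% attrition, a total sample of 285 participants will be sufficient".
- **Expected effects, same section.** The cited meta-analysis "showed a significant treatment effect in alleviating depressive symptoms (Hedges’ *g* = 0.35) and insomnia symptoms (Hedges’ *g* = 0.79". No effect is given for sleep quality, and no correlation between outcomes is given anywhere.
- **Trial design.** The design has "equal randomization (1:1 allocation ratio", so f equals half the standardised mean difference.

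**The concern.** Unqualified, Bonferroni ordinarily means the single-step method, in which every test in the family meets the same reduced level. For three tests that is 0.05/3 = 0.0167, whatever the other two show. Holm starts at 0.0167 for the smallest p-value and then relaxes to 0.025 and 0.05 as tests succeed. It needs no extra assumption about correlation and no extra data. Using plain Bonferroni for the tests therefore gives up power with no gain in familywise error control.

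Power matters here because the article reports that recruitment is complete, so it can no longer be raised by enrolling more participants. If the effects resemble those cited, insomnia will almost certainly pass first. The outcome with the smaller cited effect, depression, would still be held at 0.0167.

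**Working it through.** **Inputs.** From Sample size: evaluable N = 199, recruited N = 285, f = 0.2 for each outcome, 12 covariates, cited effects of 0.35 (depression) and 0.79 (insomnia). From Trial design: 1:1 allocation. Assumed, because the article does not give them: a family of exactly three tests, a common correlation between test statistics of 0 to 0.7, and a sleep-quality effect of d = 0.40 (varied below).

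**1. Reproduce the plan's figures.** ANCOVA F test with 1 numerator df, denominator df = N − 2 − 12, noncentrality λ = f²N. At N = 199, df = 185 and λ = 0.04 × 199 = 7.96. Power at alpha 0.05 is 80.1%, and at N = 198 it is just under 80%, so 199 reproduces. Attrition: 199 / 0.70 = 284.3, rounded up to 285, which also reproduces.

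**2. Power per outcome with Bonferroni, three tests, alpha 0.0167, N = 199.**

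- f = 0.2: λ = 7.96, power 65.7%.
- Depression, f = 0.35/2 = 0.175: λ = 0.030625 × 199 = 6.09, power 52.2%.
- Insomnia, f = 0.79/2 = 0.395: λ = 0.156025 × 199 = 31.05, power 99.9%.

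**3. Why Holm cannot do worse.** Order the p-values and compare them with 0.05/3, 0.05/2 and 0.05/1, stopping at the first failure. Every threshold is at least 0.0167, so any p-value at or below 0.0167 is rejected by both methods. For error control, suppose h of the three nulls are true. The first true null that Holm rejects is met at a threshold of at most 0.05/h, so the chance of any false rejection is at most h × 0.05/h = 5%. No correlation assumption enters.

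**4. Simulated power per outcome** (three correlated t statistics, df = N − 14, noncentrality f√N; ranges are over correlation 0 to 0.7).

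| Scenario | Outcome | Bonferroni | Holm | Gain (points) |
|---|---|---|---|---|
| N = 199, f = 0.2 on all | each | 66% | 73–75% | 7–9 |
| N = 199, cited effects, sleep quality d = 0.40 | depression | 52% | 66% | 13–14 |
| | sleep quality | 66% | 74–76% | 9–11 |
| | insomnia | 99.9% | 99.9% | 0 |
| N = 199, sleep quality d = 0.35 | depression | 52% | 63–64% | 11–12 |
| N = 199, sleep quality d = 0.79 | depression | 52% | 69% | 17 |
| N = 285, f = 0.2 on all | each | 83% | 89–91% | 5–7 |
| N = 285, cited effects, sleep quality d = 0.40 | depression | 71% | 82–83% | 11–12 |
| N = 285, sleep quality d = 0.79 | depression | 71% | 84% | 13 |

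**5. Error check.** With all three nulls true, the chance of at least one rejection is the same for both methods: 4.9% at correlation 0 and 3.9% at 0.7. The chance of at least one rejection is also identical in every other scenario, because both methods compare the smallest p-value with 0.0167. Holm's gain lies entirely in the second and third rejections.

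**The case against.** **Bonferroni is valid and standard.** This stands. A reader might infer that the plan contains an error. It does not: no statement about multiplicity is made false, and no conclusion made invalid, by naming Bonferroni. The point is one of efficiency.

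**The article does not specify single-step Bonferroni over three tests.** This also stands. A reader might infer that the plan fixes this, but the sentence follows a statement about all comparisons, and the paragraph includes secondary and paired tests. The figures above are therefore conditional on a family of three. The direction does not depend on that, since Holm is at least as powerful as Bonferroni for any family of two or more tests.

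**The sizes rest on assumptions.** A reader might take one figure as the loss, or infer that depression always loses most. Neither is supported. Under the plan's own f = 0.2 for every outcome, the gain is equal across the three. Depression gains most only when the unequal cited effects are used and sleep quality is assumed to have a larger effect than depression. Across the scenarios tabulated, the gain runs from 0 (insomnia) to 17 points (depression with sleep quality at 0.79).

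**199 is the low end of the information.** The Data analysis plan intends multiple imputation for all randomised participants and assumes 5% missing data. With 285 × 0.95 = 271 evaluable, Bonferroni power at f = 0.2 is 81%, and at 285 it is 83%. These are upper values, because imputation does not recover all lost information. The gain at 285 is smaller but does not vanish.

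**Bonferroni gives simple simultaneous intervals that match its tests.** True, and a real trade-off, since the model is meant to estimate mean differences. It has to be weighed against the power.

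**A late move to a less strict rule may look opportunistic.** This is a fair caution, because the research team is not blind to group assignment. It calls for a dated, documented change before any outcome analysis.

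**Conclusion.** The point holds as a cheap improvement. If the Bonferroni adjustment is applied in its ordinary form to the three primary between-condition contrasts, Holm gives more power at the same two-sided 5% familywise error. The gain at 199 evaluable is about 7 to 9 points on each outcome at f = 0.2. With the cited effects and sleep quality at d = 0.40, it is about 13 to 14 points on depression, 9 to 11 on sleep quality and none on insomnia. At 285 it is 5 to 7 points (f = 0.2) and 11 to 12 points for depression, up to 13 if sleep quality has d = 0.79.

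That Holm rejects at least as much with the same error control is a mathematical fact. The sizes rest on a three-test family, the ANCOVA model used for sizing, the assumed correlation and the assumed sleep-quality effect.

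Holm does not repair the mismatch between sizing at an unadjusted 0.05 and testing with an adjustment. At N = 199 and f = 0.2, power per outcome stays at 73% to 75%, below the stated 80%.

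**What to change.** In the Data analysis plan, replace the single Bonferroni sentence with wording to this effect:

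*For the three primary between-condition contrasts (change from baseline to post-intervention in sleep quality, insomnia severity and depression severity), Holm's step-down procedure will control the familywise two-sided error at 5%. The smallest p-value is compared with 0.0167, the next with 0.025 and the largest with 0.05, stopping at the first failure. Holm-adjusted p-values will be reported. The Bonferroni adjustment is retained for the secondary and the paired comparisons.*

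The last sentence is needed. Without it, the other comparisons in the paragraph would lose the only multiplicity rule they have. The change should be dated and fixed before the outcome data are analysed.

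**Cost.** A short text change and no new data. Simultaneous confidence intervals that match Holm are less simple. Bonferroni intervals can be shown alongside, with a note that an interval may include zero for a contrast that Holm rejects.
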